**Analysis of categorical outcome**
For each supportive categorical outcome, multivariable logistic regression with generalized estimating equations (GEE), allowing analysis of repeated measures, will be applied, including adjustment for baseline factors, which may contribute to the outcome variable. The model will deliver estimated adjusted odds ratio and 95% confidence interval.
Examples of supportive categorical outcomes: de novo/worsening retinopathy, nephropathy, hypertension and hypercholesterolemia.

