## Hypothesis

In patients with T2D and cardiovascular disease, a systematic, specialized multidisciplinary approach in a Cardio-Metabolic Clinic, will result in better management of diabetes and reduced cardiovascular morbidity and mortality.

Aim
This prospective, randomized controlled trial is designed to explore the benefits of a systematic, specialized multidisciplinary approach in a Cardio-Metabolic Clinic in patients with T2D and established cardiovascular disease.

Study design
The study is a single-center, open label, prospective, randomized controlled trial examining the efficacy of a specialized, multidisciplinary approach in patients with T2D and established CV disease (CVD) compared with usual care.

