# Methods

Study setting
The study will be carried out at the Cardiovascular Research Unit at OUH, Svendborg Hospital, Denmark.

Study population
Patients with T2D and established CVD, referred from general practices or seen in the outpatient clinic of Cardiology or Endocrinology at Svendborg Hospital, will undergo screening for potential inclusion in the study.

Eligibility criteria
Inclusion criteria:

- >18 years.
- Capable of giving written informed consent.
- Established diagnosis of T2D [26].
- Established heart or vascular disease, defined as either:

1. Atherosclerotic disease defined as:
   i) Prior acute coronary syndrome [27].

ii) Chronic coronary syndrome defined as the combination of: Angina pectoris AND coronary atherosclerosis assessed with either coronary CT angiography or myocardial-scintigraphy or coronary angiography AND treatment with statins and/or acetylsalicylic acid [28].
iii) Stroke [29].
iv) Peripheral arterial disease (PAD) defined as: Claudication intermittence in combination with pathological ankle brachial index AND/OR vascular PAD surgery AND/OR ischemic amputation [30]. v) Ischemic heart disease defined by one of the following criteria: a) Myocardial-scintigraphy: >10% reversibility OR b) Coronary CT angiography: Coronary Artery Calcium-score >100.

1. Heart failure (HF): HF with reduced ejection fraction, HF with Mildly reduced ejection fraction, HF with preserved ejection fraction [31].
2. Atrial fibrillation and/or flutter, including paroxysmal, persistent and chronic disease [32].
3. Valvular heart disease (which requires control in outpatient clinic of cardiology), such as aortic valve stenosis, mitral valve insufficiency, and patients with aortic dilatation.
4. Hypertension treated with at least three antihypertensive drugs.

Exclusion criteria:

1. Life expectancy less than 5 years for any reason.
2. Type 1 Diabetes Mellitus [26].
3. Participation in another clinical trial with an investigational product or device that could interfere with the primary and/or secondary endpoints of this study.

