3) Blood pressure measurement: Blood pressure will be measured at baseline and at the 3 year follow-up visit. If blood pressure is above 130/80 mmHg after 10 minutes the CMC group will measure blood pressure at home (3 times daily for 3 days) and be treated according to the Cardio-metabolic treatment algorithm. Patients in the control group will be advised to contact the general practitioner (GP) in case of blood pressure above 130/80 mmHg.

4) Ankle-brachial index (ABI): ABI will be assessed at the baseline visit and at the 3 year follow-up visit. During the procedure, patients will be instructed to lie down in a supine position and rest for a period of 10 minutes. Blood pressure measurements will be performed in both the brachial arteries and the dorsalis pedis arteries using a blood pressure cuff and a Doppler ultrasound devise. ABI will hereby be calculated.

5) Monofilament test: will be performed at the baseline visit and at the 3 year follow-up visit. This test involves applying a 10-g monofilament at the distal plantar aspect of both great toes and metatarsal joints to assess pressure sensation.

5) Transient Elastography (Fibro-scan): Patients will be evaluated for liver fibrosis using serological test with FIB-4 at baseline and at 3 year follow-up visit. Patients with high risk (FIB-4: > 2,67) or moderate risk (FIB-4: 1.3 - 2.67) at baseline and at 3 year follow-up will be referred to the department of gastroenterology for a fibro-scan. In case of suspicion of fibrosis or cirrhosis an individual risk assessment will be made by a hepatologist.

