**Three-year follow-up visit:**
At the three-year follow-up, all participants will undergo the same evaluation program as outlined during the baseline visit. They will be evaluated for clinical events related to the primary and secondary outcomes. Blood- and urine samples will be collected from all participants.

Efforts will be made to ensure that participants attend and complete the three years follow up visit. Participants will receive their appointment for this visit during the baseline visit. Additionally, they will be sent an electronic letter one month before the scheduled follow-up and will be reminded by a telephone call from the study staff.

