| To compare the occurrence of macrovascular complications, peripheral artery disease (PAD) and/or ischemic heart disease (IHD), in patients receiving optimal diabetes care in a Cardio-Metabolic Clinic versus usual care | Time to first occurrence of a composite macrovasucular endpoint comprising:   - new diagnosis of lower extremity arterial disease (LEAD), - new/progression of foot ulcers, - surgical procedures related to PAD - coronary revascularization   Surgical procedures includes: percutaneous transluminal angioplasty, peripheral artery bypass, thrombectomy, thrombolysis, amputations.  Coronary revascularization includes: percutaneous coronary intervention (PCI), coronary artery bypass graft. |
| Units of measure: Measured in count of events. | Time Frame: From baseline to 3 years of FU. |
| To compare the occurrence of macrovascular complications in the lower extremities, in patients receiving optimal diabetes care in a Cardio-Metabolic Clinic versus usual care | - Change in ankle-brachial pressure index (ABI) |
| Units of measure: Measured in ratio to baseline. | Time Frame: From baseline to 3 years of FU. |
| To compare change in protocol-driven medication in patients receiving optimal diabetes care in a Cardio-Metabolic Clinic versus usual care | Change in protocol-driven medication:   - Lipid lowering medication - Antihypertensive medication - Anti-thrombotic medication - Anti-diabetic medication - Nephro-protective medication |
| Units of measure: Measured in percentage [%]. | Time Frame: From baseline to 3 years of FU. |
| To compare change in patient experienced symptoms in patients receiving optimal diabetes care in a Cardio-Metabolic Clinic versus usual care | - Change in symptoms as reported by patients using the Kansas City Cardiomyopathy Questionnaire (KCCQ) |
| Units of measure: Measured in score points (change in percentage [%]). | Time Frame: From baseline to 3 years of FU. |
| To compare the net cost of implementing a Cardio-Metabolic Clinic in patients receiving optimal diabetes care versus usual care | - Net cost of a Cardio-Metabolic Clinic:  Cost of Cardio-Metabolic Clinic minus averted costs   Averted costs includes: averted admissions, medical treatment, and productivity). |
| Units of measure: Measured in dollars [$]. | Time frame: From baseline to 5 + 10 years of FU. |

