**Analysis of numerical outcome**
For each supportive numerical outcome, we will utilize mixed effects linear regression with included fixed effect for time point and baseline value of the outcome. For each linear mixed effects model, a random intercept will be included for each enrolled patient. These outcomes will be measured at baseline and at 3-year follow-up for the group randomized to drug optimization.
Examples of numerical outcome: changes in biochemistry from baseline to follow-up.

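### HbA1c, LDL and blood pressure are measured in both arms at baseline and 3 years, but no listed outcome compares them between arms, although the hypothesis promises better management of diabetes

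*Protocol*

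**What the plan says.** The Hypothesis section states that care in the clinic "will result in better management of diabetes and reduced cardiovascular morbidity and mortality". Management is therefore a claim in its own right, next to the clinical events.

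The Examinations section lists HbA1c, a lipid profile including LDL, and blood pressure, each at baseline and at 3 years. The section on the three-year visit covers both arms: "At the three-year follow-up, all participants will undergo the same evaluation program as outlined during the baseline visit". The Treatment algorithm section uses the same three values as triggers for adding drugs.

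The outcome table has no row for any of the three. The row closest to management reads "To compare change in protocol-driven medication in patients receiving optimal diabetes care in a Cardio-Metabolic Clinic versus usual care". It is expressed as a percentage from baseline to 3 years, over five drug groups.

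Two parts of the Statistics section add supportive outcomes:

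- **Analysis of numerical outcome:** "Examples of numerical outcome: changes in biochemistry from baseline to follow-up". The mixed model has fixed effects for time point and baseline value and a random intercept per patient. The text then says: "These outcomes will be measured at baseline and at 3-year follow-up for the group randomized to drug optimization".
- **Analysis of categorical outcome:** "Examples of supportive categorical outcomes: de novo/worsening retinopathy, nephropathy, hypertension and hypercholesterolemia". No criterion is given for new or worsening disease.

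Work-up of a raised office blood pressure differs by arm. Under Examinations, "the CMC group will measure blood pressure at home (3 times daily for 3 days" and are then treated by the algorithm, while controls are advised to see their general practitioner. The eligibility criteria describe hypertension as a qualifying condition through a drug count: "Hypertension treated with at least three antihypertensive drugs".

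**The concern.** The trial collects what it needs to show whether the clinic improves risk-factor control, but it commits to no randomised comparison of those values. If MACE turns out neutral, the listed outcomes would not show whether the clinic failed to improve control or improved it without reducing events. If MACE is reduced, the most direct link in the causal chain would rest on analyses chosen afterwards.

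Change in medication does not fill this gap. The algorithm prescribes the drugs, the intervention counts as complete once they are fully titrated, and the Ethics section itself expects treatment regimens to differ. A difference in this outcome shows that the clinic prescribed. It also has no fixed good direction, because an added antihypertensive can reflect better care or worse disease.

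**Working it through.** The protocol states no figure on this point, so there is none to reproduce. The check sets the sections side by side and adds two illustrations on stated assumptions.

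**1. What is measured against what is listed**

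| Measure | Trigger in the algorithm | Measured at baseline and 3 years | Row in outcome table |
| --- | --- | --- | --- |
| HbA1c | above 53 mmol/mol, with a described exception at 58 | yes, both arms | none |
| LDL | above 2.6, 1.8 or 1.4 mmol/L by risk group | yes, both arms | none |
| Office blood pressure | above 130/80 mmHg, or 140/85 at high biological age | yes, both arms | none |
| eGFR, UACR, FIB-4, ABI | various | yes, both arms | one each |

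The last line shows that continuous values from these visits are otherwise turned into listed outcomes.

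**2. Whether the supportive numerical outcomes close the gap**

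They do so only in part. Biochemistry plausibly includes HbA1c and LDL, but no analyte is named and blood pressure is not biochemistry. The text places the measurements in the intervention group, which contradicts the two-arm three-year visit. The stated fixed effects contain no treatment arm. A model with time point and baseline value alone estimates change over time, not a difference between arms.

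**3. Whether the sample size would support the comparison**

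The protocol gives 1500 patients at 2:1, so 1000 and 500. A loss of 13% is assumed, within its stated 10–15%: 1000 × 0.87 = 870 and 500 × 0.87 = 435. In SD units, SE = √(1/435 + 1/870) = 0.0587. Power at two-sided 0.05 is Φ(d/SE − 1.96), before any multiplicity correction:

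- d = 0.15: 0.15/0.0587 = 2.55, and Φ(0.59) = 72%.
- d = 0.20: 0.20/0.0587 = 3.41, and Φ(1.45) = 93%.

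For LDL with an assumed SD of 0.9 mmol/L and 15% loss (850 and 425), SE = 0.9 × √(1/850 + 1/425) = 0.0535. The difference detectable with 80% power is 2.8 × 0.0535 = 0.15 mmol/L.

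**4. What depends on the undefined categorical outcomes**

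Suppose the true incidence q of hypertension is the same in both arms and the outcome is defined by diagnosis or treatment. The clinic is assumed to record 90% of cases and usual care a share s. The apparent odds ratio is [0.9q/(1 − 0.9q)] / [sq/(1 − sq)]. For q = 20% and s = 60%: (0.18/0.82)/(0.12/0.88) = 1.61. The chance of a falsely significant result against the clinic, with 870 and 435 patients, is in brackets.

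| s in control | q = 10% | q = 20% | q = 30% |
| --- | --- | --- | --- |
| 60% | 1.55 (47%) | 1.61 (81%) | 1.68 (96%) |
| 80% | 1.14 (8%) | 1.15 (14%) | 1.17 (21%) |
| 90% | 1.00 (2.5%) | 1.00 (2.5%) | 1.00 (2.5%) |

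All recording rates here are assumptions. The last row is the case of equal recording. A common measured criterion at the 3-year visit would remove the difference in work-up that drives the other rows.

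**The case against.** The protocol never names medication change as the measure of better management. The table also lists retinopathy stage, kidney outcomes, FIB-4, ABI and the KCCQ. Whether uptake of guideline drugs differs is a fair secondary question in a trial of a care model, and the row is openly labelled as protocol-driven. HbA1c and LDL are named blood analyses and plausibly fall under supportive biochemistry. Details of supportive outcomes commonly belong in an SAP, which is not at hand.

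Much of this stands. Objecting to medication change as a secondary outcome would be a matter of preference, and the missing definition of a supportive example is not in itself an error.

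A reader might go further and infer that the algorithm itself produces new or worsening hypertension and hypercholesterolaemia, so that these outcomes will run against the clinic. The documents do not support that. The count of three antihypertensives is an eligibility item, not an outcome definition. For cholesterol the protocol gives only measured LDL thresholds. If measured 3-year values define these outcomes, effective treatment would lower the counts. Both are also only examples of supportive outcomes and are absent from the outcome table.

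The objection does not reach the outcome list. The protocol fixes that list, and the order of testing follows it. The organ outcomes are complications or organ measures, not control of glucose, lipids or blood pressure. The supportive biochemistry is, as worded, a single-arm analysis.

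**Conclusion.** The point holds as a gap in the outcome list, with a contradiction in the text that might otherwise have filled it. Three risk-factor values central to the algorithm are measured in both arms, and the plan as written secures no between-arm comparison of any of them. The primary MACE analysis is untouched, and no stated figure is wrong. The first half of the hypothesis, however, is left without a direct test that the data could support: about 0.15 to 0.20 SD is detectable with 72% to 93% power, under the assumed 13% loss and before multiplicity correction.

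The possible bias in the hypertension and hypercholesterolaemia outcomes is conditional. It arises only under a definition by diagnosis or drug count, and the protocol gives no definition. The odds ratios above show its possible size under assumed recording rates and are not a forecast.

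**What to change.** - Add the between-arm differences in HbA1c, LDL and office blood pressure at 3 years, each adjusted for baseline, as secondary outcomes. State which pressure is tested. Report the proportion meeting the algorithm's own stated thresholds as supportive.
- Place these rows after the existing secondary outcomes, so that the present testing order is not disturbed.
- Reconcile the numerical-outcome paragraph with the section on the three-year visit: include both arms, name the analytes, and add a treatment-arm term to the model.
- If new or worsening hypertension and hypercholesterolaemia are kept, define them by the same measured 3-year office and laboratory values in both arms, not by diagnosis, drug count or home readings.
- Keep medication change as a secondary outcome if wished, and state that it is read as a process measure.

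The cost is table wording and a few regressions on data already planned, plus three more endpoints at the end of the testing order. The protocol names both hierarchical testing and a Bonferroni-Holm correction. Late placement fully protects the earlier outcomes only under the hierarchy; if Holm is applied across the whole list, the added tests would make its thresholds somewhat stricter.

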**Testing and confounders**
The statistical test will be performed in a hierarchical order according to the succession of the objectives. The p-value will be corrected with the Bonferroni-Holm method.
Potential effect modifiers are: Sex, age, baseline treatment regime, and baseline comorbidities.

# Ethics and dissemination

**Ethics**

The study complied with the Declaration of Helsinki, and was approved by the local ethics committee (Project-ID: S-20230015). When participating in this study, the intervention will consist of an intensive effort in diabetes care based on the most recent guidelines and recommendations. Whereas, the control group will receive the standard of care from their regular physician(s). Therefore, in theory, the treatment should be the same, and we do not anticipate any associated risks. However, we anticipate that a comprehensive evaluation and examination will lead to significant differences in the treatment regimen. Considering this, we expect a therapeutic gain, both in CVD death and diabetic microvascular complications for the participants receiving the intervention. The participants in the control group will receive the standard of care, thus, there are no ethical considerations.
The local ethical committee will be notified of a protocol amendment if any changes to the research project could potentially affect the participants.

The national patient insurance will cover the participants. No compensation or remuneration will be provided for participation in the study.

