## Treatment algorithm:

**Figure 3. Overview of the treatment algorithm in the CMC**

**
[figure not shown]
**

- Dyslipidemia:
  Dyslipidemia is assessed by LDL status in blood samples. Patients are classified according to table 1 (32). Patients with moderate CV risk; will be recommended a LDL <2.6 mmol/L.
  Patients with high CV risk; will be recommended a LDL <1.8 mmol/L.
  Patients with very high CV risk; will be recommended a LDL <1.4 mmol/L (32).

If LDL exceed these thresholds, the treatment algorithm will be according to the following order: 1) High dose Atorvastatin, 2) Ezetimibe, 3) Referral to lipid-clinic.

- Hypertension:
  Blood pressure is measured in the examination, patients with a blood pressure >130/80 mmHg are instructed in measurement of blood pressure at home 3 times a day for three days (32). If the mean home blood pressure is >130/80 mmHg, treatment algorithm will be according to the following order:

1) ACE-inhibitor or angiotensin II receptor blocker (ARB), 2) thiazide, 3) calcium antagonist, 4) mineralocorticoid (MRA), and 5) beta blocker. If aforementioned is already supplied 6) Referral to hypertension-clinic.

In patients with a high biological age blood pressure <140/85 mmHg is accepted. Blood pressure >140/85 mmHg the above-mentioned treatment algorithm will be followed (32).

- Thrombosis prophylaxis:
  Patients with ischemic heart disease are recommended lifelong acetylsalicylic acid.
  If patients have had a new acute myocardium infarction, they will be prescribed 12 months of ADP-receptor blocker (32).

Patients with cerebrovascular disease are recommended lifelong clopidogrel treatment(32) . Patients with periphery arterial disease are recommended lifelong ASA treatment (32).

Patients with atrial fibrillation/flutter are recommended lifelong direct oral anti-coagulant (DOAC) treatment (32).

When two antithrombotic drugs are used, proton pump inhibitors are recommended to prevent gastrointestinal bleeding(32).

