- Diabetes: Hyperglycemia is assessed by measurement of HbA1c. If HbA1c > 53 mmol/mol addition of antidiabetic treatment is required (32). Exceptionally, in patients with a long diabetes duration (>10 years), high age (> 65 years), and episodes with hypoglycemia, a HbA1c <58 mmol/mol will be accepted (33, 34). The standard treatment algorithm will be according to the following order: 1) Biguanides 2) SGLT2 inhibitor, 3) GLP-1 receptor agonists 4) Insulin. In patients with atherosclerotic cardiovascular (ASCVD) treatment with a SGLT2 inhibitor and/or GLP-1 receptor agonist will be first. If insulin treatment is required, an endocrinologist will be contacted.
- Microvascular complications: - Nephropathy: Defined by reduced eGFR <60 ml/min and/or increased urine albumin/creatinine ratio (UACR) >30mg/g. Patients will be treated with maximum tolerable dosis of 1) ACE-inhibitor/ARB and SGLT2 inhibitor. 2) Finerenone, if 1) is fulfilled and either: eGFR>60 ml/min + UACR 300 mg/g or eGFR< 60 ml/min + UACR >30 mg/g (32).
  If further assessment of nephropathy is required, a nephrologist will be contacted.

- Retinopathy: Compliance with ophthalmologist check-ups. If non-obedient referral to ophthalmologist check-up.

- Evaluation of liver fibrosis: Systematic screening using serological test with FIB-4 will be performed at baseline and at the 3 years follow-up visit. Patients with moderate risk (FIB-4: 1.3 - 2.67) at baseline and at 3 years follow-up and patients with high risk (FIB-4: > 2,67) will be referred to the department of gastroenterology for a Fibro-scan. In case of suspicion of fibrosis or cirrhosis an individual risk assessment will be made by a hepatologist.

- Evaluation of prescription of SGLT2 inhibitor and/or GLP-1 receptor agonist:
  SGLT2 inhibitor will be prescribed if one of the following are present (32) :

1. Heart failure (regardless of ejection fraction)

2. Chronic kidney disease

3. Atherosclerotic heart disease

4. In patients with a high or very high CV risk (table 1).

GLP-1 receptor agonists will be prescribed if one of the following are present (32):

1. If further hyperglycemic control is needed on top of treatment with Biguanid and/or SGLT2-i.
2. In patients with a very high CV risk (table 1).

3. Preferences towards further weight loss (BMI>35).

- Lifestyle:

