**Five year follow-up:**
A journal audit and look-up in the Danish Health Data Authority will be performed to examine the number of clinical events according to the primary and secondary endpoints.

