## Discontinuation:

Participants will be followed for the complete duration of the study regardless of their adherence to the study intervention. Any component of the study intervention may be discontinued at the discretion of either the participant or the study staff due to safety, behavioral or compliance reasons.

Withdrawal of consent: Participant may withdraw consent at any time upon request. Those considering withdrawal should be offered the option of flexible participation, if feasible. If a participant withdraws consent, any data collected before such a withdrawal of consent may still be used for study purposes. Participants who withdraw will be included as intention-to-treat in the statistical analysis once the study ends.

Lost to follow up: If participants fail to attend and complete the three years follow up visit, they will be considered lost to follow-up for the analysis of the secondary outcomes that requires attendance. However, these participants will still be included in the primary and secondary prognostic outcomes.

Timeline
The study started in January 2024, with a four-year inclusion period that will continue until January 2028. After three years, all patients will have a follow-up visit and baseline assessments will be repeated. Clinical events will be assessed at 5- and 10-years follow-up by journal audits and by look-up in the Danish Health Data Authority. Thus, the 5 years follow-up will be approximately in January 2031, and 10 years follow-up in January 2036 (figure 4).

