**Figure 4 - Timeline for the study**

[figure not shown]

Outcomes The primary outcome is the time to the first occurrence of a composite of CV deaths, non-fatal myocardial infarction, non-fatal stroke, and hospitalization for heart failure.

The secondary outcomes are the time to the first occurrence of one of the single components of the primary outcome, and a combination of the single components of the primary outcome to assess the total symptom burden. Additional secondary outcomes will be the assessment of microvascular complications, protocol driven medical changes and a cost-effectiveness analysis of the Cardio Metabolic Clinic. Primary and secondary outcomes and endpoints are shown in the following table:

| **Primary outcomes** | **Primary endpoints** |
| --- | --- |
| To examine whether patients with type 2 Diabetes (T2D) receiving optimal diabetes care in a Cardio-Metabolic Clinic are superior compared to usual care in reducing; incidence of cardiovascular (CV) death, non-fatal acute myocardial infarction (AMI), non-fatal stroke, and hospitalization for heart failure (HF) | Time to the first occurrence of major adverse cardiovascular event (MACE), a composite endpoint consisting of:   - CV death - Non-fatal AMI - Non-fatal stroke - Hospitalization for HF |
| Units of measure: Measured in days. | Time frame: From baseline to 5 years of follow-up (FU). |

| **Secondary outcomes** | **Secondary endpoints** |
| --- | --- |
| To examine whether patients with type 2 Diabetes (T2D) receiving optimal diabetes care in a Cardio-Metabolic Clinic are superior compared to usual care in reducing; incidence of cardiovascular (CV) death, non-fatal acute myocardial infarction (AMI), non-fatal stroke, and hospitalization for heart failure (HF) | Time to the first occurrence of MACE, a composite endpoint consisting of:   - CV death - Non-fatal AMI - Non-fatal stroke - Hospitalization for HF |
| Units of measure: Measured in days. | Time frame: From baseline to 10 years FU. |
| To compare the individual component, CV death, of the primary endpoint in patients receiving optimal diabetes care in a Cardio-Metabolic Clinic versus usual care. | Time to the first occurrence of:   - CV death   (Presumed cardiac condition leading to death. Including: AMI, venous thromboembolic event, malignant arrhythmia, cardiogenic shock, fatal stroke and aorta dissection) |
| Units of measure: Measured in days. | Time frame: From baseline to 5 + 10 years of FU. |

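### All-cause death, bleeding, severe hypoglycaemia and non-fatal haemorrhagic stroke are not declared outcomes, although one arm has its drug treatment intensified

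*Protocol*

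**What the plan says.** The Ethics section reasons from equal treatment: "Therefore, in theory, the treatment should be the same, and we do not anticipate any associated risks". It continues: "However, we anticipate that a comprehensive evaluation and examination will lead to significant differences in the treatment regimen". It then expects a gain in cardiovascular death and microvascular complications for the clinic arm.

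The Interventions section regards the programme as complete when each suggested treatment has reached its target or highest tolerated dose. The treatment algorithm covers antithrombotic, antihypertensive and glucose-lowering drugs, among others. Under thrombosis prophylaxis it states: "When two antithrombotic drugs are used, proton pump inhibitors are recommended to prevent gastrointestinal bleeding". Under diabetes, the conditions for accepting a higher HbA1c include "high age (> 65 years), and episodes with hypoglycemia". The Discontinuation section allows any component to be stopped "due to safety, behavioral or compliance reasons".

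In the outcomes table, death appears as cardiovascular death, described as "Presumed cardiac condition leading to death", and as renal or cardiovascular death within the kidney composite. The non-fatal stroke row lists thromboembolic and undetermined types. The statistics section plans a mortality analysis for cardiovascular causes only. The five-year follow-up is a journal audit and register look-up "to examine the number of clinical events according to the primary and secondary endpoints", and the ten-year follow-up has the same scope.

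**The concern.** The intervention is intensified drug treatment in one arm of an open-label trial. The declared clinical-event outcomes are mainly events that this treatment should prevent. The harms that the algorithm itself touches on are not declared, and neither is death from any cause.

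Two things are at stake. First, if MACE fell while bleeding, severe hypoglycaemia or non-cardiovascular deaths rose, the plan has no between-arm comparison that puts the two side by side. Second, cardiovascular death rests on a presumed cause in an unblinded trial. All-cause death needs no attribution of cause and is the natural check, but it is not planned.

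This is not a matter to leave to a statistical analysis plan. Which outcomes are declared, and which data are requested from the registers, is protocol content. An analysis plan cannot analyse events that were not requested.

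**Working it through.** There is no figure in the protocol to reproduce. The check is a comparison of sections, followed by a calculation of what the added outcomes could show.

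**1. Events against the outcomes table**

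| Event | Where the protocol touches it | Declared outcome |
| --- | --- | --- |
| Bleeding | Treatment algorithm, thrombosis prophylaxis | None |
| Hypoglycaemia | Treatment algorithm, diabetes | None |
| Non-fatal haemorrhagic stroke | Algorithm recommends antiplatelet and anticoagulant drugs | Not listed in the non-fatal stroke row |
| Death from any cause | Not addressed | None; only cardiovascular death, or renal or cardiovascular death |

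**2. Data collection.** The 5- and 10-year look-ups follow the primary and secondary endpoints. What is not in the table is not part of the stated request. Individual visits are arranged after a new prescription that needs monitoring, so harms noted there would come mainly from the clinic arm and would not give a fair comparison. The register look-up covers both arms alike and is the right source.

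**3. The Ethics sentences.** The absence of risk is derived from sameness of treatment, and the expected gain is derived from difference in treatment. If the regimens differ enough to produce benefit, sameness cannot be the ground for expecting no risk.

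**4. What the added outcomes could show.** The target of 1500 at 2:1 gives 1500 × 2/3 = 1000 clinic and 1500 × 1/3 = 500 control participants. The control risks below are assumptions, since the protocol gives none. For a two-sided 5% test of two proportions:

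power = Φ[(d − 1.96 × SE0) / SE1]

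Here d is the risk difference, SE0 uses the pooled risk and SE1 the two separate risks. For a doubling from 1% to 2%:

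- pooled risk = (5 + 20)/1500 = 0.01667
- SE0 = √(0.01667 × 0.98333 × (1/500 + 1/1000)) = 0.00701
- SE1 = √(0.01 × 0.99/500 + 0.02 × 0.98/1000) = 0.00628
- (0.01 − 1.96 × 0.00701)/0.00628 = −0.60, so power is about 28%

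The same calculation for other assumed control risks:

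| Control risk | Power for a doubling |
| --- | --- |
| 0.5% | 14% |
| 1% | 28% |
| 2% | 53% |
| 5% | 93% |

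For all-cause death, the standard error of the log hazard ratio with D deaths at 2:1 is about 1/√(D × 2/9). The 95% interval is the estimate divided and multiplied by exp(1.96 × SE). Assume that 10% to 30% of 1500 die:

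- D = 150: SE = 1/√33.3 = 0.173, factor exp(0.339) = 1.40
- D = 450: SE = 1/√100 = 0.100, factor exp(0.196) = 1.22

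All-cause death would therefore carry useful information. Rare harms would be estimated with wide intervals.

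**The case against.** The strongest reply is that harm is not invisible under the present plan. QALYs at 5 and 10 years are declared and cannot be computed properly without all deaths. A cumulative incidence function ordinarily treats other deaths as a competing event. Change in eGFR, the kidney composite and the KCCQ could reveal renal or symptomatic worsening, and fatal stroke counts as cardiovascular death. This stands, and it limits the point. A reader might infer that harm from the algorithm cannot be seen at all, or that a fatal bleed is counted nowhere; the documents do not support that. These measures are partial and indirect, however. None of them shows a difference in bleeding, severe hypoglycaemia or non-cardiovascular death as such.

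A second reply is that bleeding and hypoglycaemia appear as things to prevent or to allow for, not as declared risks of the trial. That is correct. It still shows that the protocol foresees them. Likewise, the Ethics text says in theory and then openly turns to practice, so its contrast is deliberate. The ground given for expecting no risk is nevertheless withdrawn in the next sentence.

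Three further inferences should not be drawn:

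- **Net cost.** The row says "Averted costs includes: averted admissions, medical treatment, and productivity". This might be taken to leave out admissions caused by treatment. It can equally be read as a net difference between arms, in which such admissions reduce the amount averted.
- **Size of harm against benefit.** Setting an excess harm rate beside the planned 15% reduction might suggest that the two are of similar size. The protocol gives no harm rate and no event rate, and does not say whether the 15% is relative, so any such comparison would be made of assumptions.
- **Completeness of the event lists.** The cardiovascular-death and stroke lists are introduced as inclusions and may not be exhaustive. The exact statement is that haemorrhagic stroke is not listed in the non-fatal row, not that it is excluded.

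Finally, low power for rare harms is a real limit of the remedy. It argues for reporting estimates with intervals, not for leaving the outcomes undeclared.

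**Conclusion.** The point holds as a gap in the declared outcomes and the data request. All-cause death, bleeding and severe hypoglycaemia have no row, and non-fatal haemorrhagic stroke is not listed. The look-ups follow the listed endpoints, and no cause-free mortality outcome supports a presumed cardiovascular cause of death in an open-label trial. Fewer MACE could not be weighed against these events as a planned comparison.

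This conclusion rests on the protocol text alone and needs no assumed rate. The amount of harm that might go uncounted cannot be derived from the documents and is not claimed here. The power and interval figures rest on assumed risks and full enrolment of 1500; they describe only how informative the added outcomes would be. The gap should be closed, because closing it is cheap and changes what the trial can conclude.

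**What to change.** 1. Add two between-arm outcomes, from randomisation to 5 and 10 years: (a) all-cause death; (b) register-coded major bleeding, including fatal bleeding and haemorrhagic stroke, and severe hypoglycaemia, reported per item.
2. Take them from the same register look-up in both arms, and widen the data request in the five- and ten-year follow-up sections to match.
3. Report them as estimates with 95% confidence intervals, outside the hierarchical order and the Bonferroni-Holm correction in the Testing and confounders section. The existing tests are then unaffected.
4. Reconcile the two adjacent sentences on risk and on differing regimens in the Ethics section.

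The cost is a few more codes in an extraction already planned, two outcome rows and a short amendment. There is no change in sample size and no additional visit. The downsides are wide intervals for rare harms and a benefit claim that may look less favourable. None of this alters a dose or a clinical rule.
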